## Abstract

**Background:**

Acute coronary syndromes (ACS) often cause rapid decline in renal and cardiac function. In patients with ACS, combined renal dysfunction is associated with increased overall mortality and cardiovascular events. Physical activity (PA) management may crucially contribute towards protection of renal function in patients with ACS. This article describes the study protocol of a randomized controlled trial (RCT) assessing whether online support for PA management using wearable devices and information communication technology for patients with ACS facing difficulties in participating in outpatient cardiac rehabilitation after discharge can protect renal function following disease onset.

**Methods:**

We have designed a two-arm RCT with a 3-month follow-up period. The online support intervention incorporates monitoring of PA, pulse rate, and blood pressure using a wearable device with an accelerometer and a web application system, as well as periodic educational feedback and goal setting. The primary study endpoint is the estimated glomerular filtration rate based on serum cystatin C (eGFRcys). The intervention effect will be assessed using the eGFRcys at 3 months adjusted for baseline values. The secondary endpoints are the urine albumin/creatinine ratio, brain natriuretic peptide levels, average step count, peak oxygen uptake, quality of life, and incidence of adverse events.

**Discussion:**

This RCT will provide evidence regarding the effectiveness of online support for PA management as a renal protection strategy following ACS onset. This novel strategy not only mitigates barriers impeding participation in outpatient cardiac rehabilitation and protects cardiac and renal function in patients with ACS, but also may contribute towards improving survival and recurrence rates, preventing dialysis, and reducing medical and long-term care costs.

**Trial registration::**

The trial was registered in the Japan Registry of Clinical Trials on July 5, 2024. The registration number is jRCT1022240014 (Impact of Online Support of Physical Activity Management Using a Wearable Device on Renal Function in Patients with Acute Coronary Syndrome).

## Introduction

Acute coronary syndromes (ACS), including acute myocardial infarction, often cause rapid decline in renal and cardiac function (Hillege et al., 2003; Eijkelkamp et al., 2007; Esmeijer et al., 2018). Further, approximately 30% of patients with ACS develop new-onset renal dysfunction, with 40% of them progressing to chronic kidney disease (CKD) (Marenzi, Cosentino & Bartorelli, 2015). Among patients with ACS, combined renal dysfunction is associated with increased overall mortality and cardiovascular events (Anavekar et al., 2004; Okina et al., 2021). Therefore, it is important to maintain both cardiac and renal function after onset of ACS. However, there remain no established interventions for preventing renal dysfunction after onset of ACS.

Cardiac rehabilitation (CR) has been shown to improve exercise capacity, coronary risk factors, and quality of life (QOL), as well as reduce cardiovascular recurrence and overall mortality. Further, numerous guidelines recommend CR as a Class I procedure for managing ST-elevation myocardial infarction (O’Gara et al., 2013; Amsterdam et al., 2014; Ibanez et al., 2018; Kimura et al., 2019; Makita et al., 2022). Moreover, recent studies have demonstrated that CR centered on supervised exercise program maintained or improved renal function in patients with ACS (Takaya et al., 2014) or cardiovascular disease (CVD) (Toyama et al., 2010; Fujimi et al., 2015; Iso et al., 2015; Kimura et al., 2015; Hama et al., 2018; Sasamoto et al., 2021; Hama et al., 2022). Takaya et al. (2014) reported that late phase II CR of patients with ACS and comorbid CKD improved exercise tolerance, cardiac-related markers such as B-type natriuretic peptide (BNP), and estimated glomerular filtration rate (eGFR). Similarly, several observational studies have demonstrated that CR helps maintain or improve eGFR or urinary protein levels in patients with CVD (Toyama et al., 2010; Fujimi et al., 2015; Iso et al., 2015; Kimura et al., 2015; Hama et al., 2018; Sasamoto et al., 2021; Hama et al., 2022). This suggests that renal function in patients with CVD may be a novel therapeutic target for CR; however, this remains to be validated by randomized controlled trials.

Previously, we have examined the association between physical activity (PA) and changes in renal function in patients with ACS undergoing late phase II CR and found that a daily step count (approx. 5,000 steps/day) and moderate-to-vigorous PA (>3.0 METs) could improve the eGFR (Sato et al., 2019; Sato et al., 2021; Sato et al., 2024). Moreover, PA has been shown to improve renal function in patients with ACS with and without complicated CKD. Furthermore, exercise intolerance in patients with ACS is an independent predictor of more rapid decline in renal function (Sato et al., 2023). Accordingly, CR interventions that improve exercise tolerance and PA may be effective strategies for protecting renal function.

However, there are serious limitations in providing outpatient CR after the onset of ACS. For example, the participation rate in phase II CR among outpatients after ACS in Japan is extremely low at 18% (Arakawa et al., 2016). Factors that influence participation in exercise programs include external factors (safety, transportation, social support), internal factors (physical function, cognitive function, and emotions), and cultural factors (Campkin, Boyd & Campbell, 2017). In Japan, the percentage of patients with ACS who were recommended CR by their primary physician is as low as 32% (Ohtera et al., 2017). Despite the high level of evidence for CR, the low participation rate of CR has remained unchanged worldwide.

On the other hand, PA monitoring interventions based on wearable devices such as pedometers have been found to contribute to improvements in PA and mitigating cardiovascular risk in patients with ACS (Houle et al., 2011; Houle et al., 2013). Recent reports have described the effectiveness of remote CR using wearable devices as an alternative to traditional center-based CR. Remote CR, which allows participation in CR without hospital visits, has several advantages such as eliminating the time required to visit the hospital, solving access problems among patients living far from the hospital, potentially reducing costs, avoiding the risk of infection during group exercise, and conferring the benefits of information technology equipment (Nakayama et al., 2023). Previous meta-analyses have shown that remote CR can effectively improve exercise tolerance and prognosis, and it is equally or more effective in improving PA levels, QOL, adherence, lipid metabolism, blood pressure, and hospital readmissions compared with center-based CR (Rawstorn et al., 2016; Ramachandran et al., 2022; Zhong et al., 2023). Specifically, remote PA monitoring using wearable devices may be a novel CR strategy that can be adopted by more patients with ACS since it eliminates time and location constraints, as well as provides real-time patient information and objective feedback. This intervention has the potential for effectively improving the motivation and adherence in patients with ACS to PA management. However, the effect of remote support for PA management using wearable devices on improving renal function in patients with heart disease remains unclear.

We hypothesize that remote support for PA management using wearable devices and information communication technology for patients with ACS who have difficulty participating in outpatient CR may protect renal function after the onset of ACS.

### Objective

The primary objective of this study is to determine the impact of remote support for PA management using a wearable device on renal function in patients with ACS. The secondary objectives are to determine the impact of this intervention on other factors such as cardiac and physical function as well as QOL, and to determine whether it can be an alternative intervention for patients with ACS who have difficulty participating in outpatient CR.

### Clinical implications

This study will provide evidence regarding the effectiveness of remote support for PA management in renal protection after ACS, which may improve survival and recurrence rates, prevent dialysis, and reduce medical and nursing care costs for patients with ACS. The validation results of this study will provide important scientific information for establishing a novel CR strategy that can be adopted by many patients with ACS who have difficulty participating in outpatient CR.

## Methods

### Study design

The study design will be an open-label, two-arm, parallel, randomized control trial (Fig. 1). The study protocol conforms to the 2017 CONSORT NPT Extension and the study intervention is described in accordance with the CONSORT-EHEALTH.

**Figure 1 fig-1:**
[figure not shown]
Randomized controlled trial design and flowchart. Patients with ACS who cannot participate in center-based CR for any reason are enrolled. Patients in both groups receive usual care. The online support intervention incorporates monitoring of physical activity, pulse rate, and blood pressure using a wearable device with accelerometer and a web application system, as well as periodic educational feedback and goal setting. ACS, acute coronary syndromes; CR, cardiac rehabilitation.

### Ethics approval

This study received approval from the Ethics Committee of Fukushima Medical University (Approval No. REC2023-174).

### Study eligibility and recruitment

The inclusion criteria for patients in this study are as follows: (i) patients with ACS who underwent percutaneous coronary angioplasty and inpatient CR, (ii) age ≥18 years at the time consent was obtained, (iii) inability to participate in outpatient CR after discharge, (iv) having a smartphone, and (v) agreeing to participate in this study after receiving verbal and written explanations from the researchers. Written consent was obtained from all participating patients in this study. The exclusion criteria are as follows: (i) lack of independence in activities of daily living, (ii) unstable angina, (iii) uncontrolled arrhythmia causing hemodynamic abnormalities, (iv) severe valvular disease, (v) uncontrolled diabetes, (vi) other diseases that contraindicate the use of exercise therapy, (vii) undergoing dialysis, (viii) other acute diseases or indications for surgical treatment, (ix) dementia, and (x) inability to make regular outpatient visits to the study site after discharge.

Researchers in Southern Tohoku General Hospital and Ohta Nishinouchi Hospital, which are the institutions conducting the study, will recruit study participants who have the potential to meet the eligibility criteria. The principal investigator of Fukushima Medical University, which is the institution responsible for the research, will oversee and manage patient enrollment.

### Randomization and blinding

Randomization allocation will be performed on the web using the UMIN INDICE cloud (https://www.umin.ac.jp/indice/cloud.html). Allocation will be completed within 2 weeks of initiation of inpatient CR. This study will not be blinded. Adjustment factors for allocation will be age (<60 years *vs.* ≥60 years), sex (male *vs.* female), and highest creatine kinase level (<3,000 U/L *vs.* >3,000 U/L).

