### Intervention

Online support for PA management will begin at the time of discharge; additionally, patients in the intervention group will manage their own PA based on educational support provided by the physical therapist under the supervision of the primary physician (Fig. 2). The physical therapist administering the intervention must have ≥1 year of experience in physical therapy for patients with CVD, including ACS, or be a registered instructor of CR by the Japanese Association of Cardiac Rehabilitation (https://www.jacr.jp/en/).

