### Online support for PA management

Patients in the intervention group will receive a wrist-worn wearable device (Fitbit Inspire 3, Fitbit, Inc, San Francisco, CA, USA) after assignment, and a web application (Recaval, SapplyM, Inc., Tokyo, Japan) for PA management will be downloaded to their smartphones. Data regarding PA and pulse rate obtained from the wearable device will be transmitted in real time *via* the application to the tablet device of the physical therapist in charge of the research facility. The wearable device is designed to locally store data until an internet connection is available. In addition to this biometric monitoring, the web application has chat and report feedback functions that allow two-way communication between patients and medical professionals. Patients will be instructed to wear the wearable device unless they are bathing or charging the device. Moreover, patients will be instructed to enter their daily blood pressure and self-records of subjective symptoms into the application, which will also be monitored daily by the physical therapist. Using this web application, patient information is completely anonymized; each patient is assigned a specific ID. In addition, this web application has a robust access restriction function. Only the interventionists at each research facility are only given access to the patient data of their own institution and have no access to the patient data of other research institutions.

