At the beginning of the intervention and at 2-week intervals thereafter, the physical therapist will provide the patient with a summary report of daily vital sign data, including educational comments and praise commending the achievement of PA and activity pulse rate goals, through the app. Regarding the target PA value, which is the basis of the educational support, the patients will be assigned a target of ≥5,000 daily steps, referring to a previously reported cutoff value for the number of steps per day that affects improvement of renal function in patients with ACS (Sato & Kohzuki, 2021; Sato et al., 2021). Further, this target can be achieved without worsening of vital signs or subjective symptoms. For example, if the weekly average daily step count is <5,000 steps/day, a smaller target of 1,000 steps/day is set for the next week and thereafter, which allows the patient to achieve the goal of ≥5,000 steps/day in incremental stages. As a safety management measure, the target values for pulse rate during activity and duration of activity above moderate intensity are set according to each patient’s results of the baseline cardiopulmonary exercise test and Karvonen’s formula (Makita et al., 2022). Table 1 shows the criteria for discontinuation of the intervention.

**Table 1 table-1:** Criteria for discontinuation of the intervention.

Criteria
(1) Cardiac arrest, severe bradycardia, fatal arrhythmia (ventricular tachycardia/ventricular fibrillation), or symptoms that cannot be ruled out during follow-up
(2) In case of sudden deterioration of vital signs or subjective symptoms (severe chest pain, abdominal pain, back pain, epileptic seizure, loss of consciousness, hypotension, severe joint pain, muscle pain, *etc*.).
(3) Accidents (falls, falls, bruises, trauma, *etc*.)
(4) In case of persistent hypertension (systolic blood pressure ≥ 250 mmHg or diastolic blood pressure ≥ 115 mmHg) or hypotension (systolic blood pressure < 80 mmHg) that is difficult to control.
(5) Deterioration of consciousness during follow-up
(6) The attending physician determines that the intervention should be discontinued due to changes in the patient’s condition or treatment strategy during follow-up
(7) The patient is hospitalized
(8) The patient wishes to discontinue the intervention.

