### Outcome assessment

Table 2 describes the outcome measures for this trial. Patient characteristics and baseline measurements will be assessed at discharge (∼2 weeks after the onset of ACS) and reassessed after 3 months.

The primary outcome of this study will be the eGFR based on serum cystatin C (eGFRcys). In general clinical practice, the eGFR based on serum creatinine is widely used as an index for assessing renal function. However, PA, including exercise, can alter serum creatinine levels *via* changes in skeletal muscle mass. Therefore, cystatin C, which is independent of skeletal muscle mass, is preferred when examining the effects of PA on renal function (Séronie-Vivien et al., 2008; Poortmans et al., 2013). The eGFRcys will be estimated using the Japanese Society of Nephrology equation as follows:

eGFRcys (mL/min/1.73 m^2^) = 104  × Cystatin C^−1.019^ × 0.996^Age^ × 0.929 (if female)–8 (Horio et al., 2013).

This study will perform between-group comparisons of eGFRcys at 3 months adjusted for baseline values. eGFR decline after ACS may be particularly steep during the first 90 days after onset (Hillege et al., 2003). It is important to examine the inhibitory effect on eGFR decline during this period; accordingly, we set a 3-month follow-up period for this study. Most previous studies on the impact of outpatient CR on eGFR have similarly set a 3-month intervention and observation period (Toyama et al., 2010; Takaya et al., 2014; Hama et al., 2018; Sasamoto et al., 2021; Hama et al., 2022). Therefore, the follow-up period can be considered reasonable.

**Table 2 table-2:** All outcome measures and assessment schedule for this study. CPET, cardiopulmonary exercise test; EQ-5D-5L, Euro QOL 5-dimensions 5-levels; eGFRcreat, estimated glomerular filtration rate calculated from serum creatinine; eGFRcys, estimated glomerular filtration rate calculated from serum cystatin C; LPA, light-intensity physical activity; MPA, moderate-intensity physical activity; QOL, quality of life; SB, sedentary behavior; VPA, vigorous-intensity physical activity.

	Baseline	3-month
**Characteristics**: sex, age, alcohol consumption history, smoking history, location of coronary artery stenosis, Killip classification, contrast fee, medical history, comorbidities, echocardiography, length of hospital stay, height	•	
**Body conditions:** weight, body mass index, resting blood pressure, resting pulse rate	•	•
**Physical function:** CPET and grip strength	•	•

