**Medication**		
**Adverse events**		
(Intervention group only) ** Fitbit data:** daily sleep time and heart rate (maximum, minimum, and average)		

Secondary outcomes will include the urine albumin/creatinine ratio (ACR), BNP, average step count, peak oxygen uptake (VO2) based on a symptom-limited cardiopulmonary exercise test (CPET), Euro QOL 5-dimensions 5-levels, and incidence of adverse events. In addition, blood biochemical analysis data such as urea nitrogen; albumin; triglycerides; high- and low-density cholesterol; hemoglobin; and blood glucose will be collected. These outcome measures will be assessed concurrently with the primary evaluation. In the symptom-limited CPET, to avoid overloading the cardiovascular system after ACS, the exercise load is terminated when the gas exchange ratio reaches 1.2, which is defined as the peak point, even before reaching the symptom limit (Sato et al., 2023).

PA assessment will be performed immediately after discharge and after 3 months for a 7-day period. The Active Style Pro HJA-750 (Omron Healthcare Company; Kyoto, Japan), which has a 3-axis accelerometer that has been validated and shown to be highly reliable (Oshima et al., 2010; Ohkawara et al., 2011), will be used to evaluate PA and the average number of steps. Sedentary behavior, light-intensity PA, moderate-intensity PA, and vigorous-intensity PA will be defined as PA of ≤1.5 metabolic equivalents (METs), >1.5 and <3.0 METs, ≥3.0 and <6.0 METs, and >6.0 METs, respectively (Bull et al., 2020); moreover, the time spent wearing the device will be collected. To avoid the impact of checking PA on increasing PA levels, the researcher sets the device to prevent displaying the PA data. The patients will be instructed to wear the accelerometer at all times except when sleeping and bathing. If the time the device is worn is <10 h per day, activity data for that day will be excluded. The minimum number of days required for evaluation is defined as “4 days or more”, which is more than half of the 7 days (Fig. 3). Patients will return the accelerometer to the hospital by mail at the end of that 7-day PA measurement period. The principal investigator at each hospital will transfer PA data from the accelerometer to the computer *via* a reader (HHX-IT4, Omron Healthcare Company; Kyoto, Japan).

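### The allocation window lets baseline exercise-test and EQ-5D values be taken after the arm is known, and the step-count baseline is always recorded after the intervention has begun

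*Protocol article*

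**What the plan says.** Under Randomization and blinding, the protocol article states "Allocation will be completed within 2 weeks of initiation of inpatient CR" and "This study will not be blinded". Under Online support for PA management, "Patients in the intervention group will receive a wrist-worn wearable device" once they have been assigned, and the web application is put on their smartphones.

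The baseline has a different anchor. Under Outcome assessment, "Patient characteristics and baseline measurements will be assessed at discharge", which is put at roughly two weeks after onset. Under Intervention, "Online support for PA management will begin at the time of discharge".

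Step count has its own schedule, given in the text after Table 2: "PA assessment will be performed immediately after discharge and after 3 months for a 7-day period".

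Under Statistical analysis, the primary eGFRcys and the secondary ACR, BNP, step count, peak VO2 and EQ-5D are all analysed by ANCOVA with the baseline value as covariate. Adverse events are compared by a chi-square test. The analysis is declared to be by intention to treat, and the only provision for dropouts concerns their 3-month data.

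**The concern.** ANCOVA on a baseline value gives an unbiased treatment effect only if allocation cannot influence that value. The simplest guarantee is to record baseline before allocation. Here the two events hang on different clocks, and the stated clocks allow allocation days before baseline. In an open-label trial, knowing the arm could change how hard a patient works in an exercise test, when a tester ends it, or how a patient rates their own health. Any arm difference created this way carries through to the adjusted effect, multiplied by the regression slope.

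The second consequence is a gap. A patient who is allocated and then transferred, worsens or withdraws before discharge has no covariate, and an ANCOVA on complete cases leaves that patient out.

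For step count, the covariate is not merely open to influence by knowledge of the arm: it is recorded while the intervention is running.

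**Working it through.** **1. The plan's own figure.** The inputs, from Sample size calculation, are f = 0.3125, alpha 0.05, power 0.80, two groups and one covariate. For an F test with 1 and N − 3 degrees of freedom and noncentrality f²N, the smallest N reaching 0.80 is 83 (noncentrality 0.3125² × 83 = 8.11; power 0.803). Then 83 / 0.95 = 87.4, rounded up to 88. Both stated figures reproduce. The order of baseline and allocation changes neither. The f is used here only as the protocol states it; whether it is the right effect size is a separate question.

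**2. The timing rules side by side.**

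| Event | Anchor in the article |
|---|---|
| Allocation | Up to two weeks after inpatient rehabilitation starts |
| Device and app | After assignment |
| Baseline blood, urine, exercise test, grip strength, EQ-5D | Discharge, about two weeks after onset |
| Online support | Starts at discharge |
| Baseline step count | Seven days immediately after discharge |

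Support starts at discharge, so an intervention patient must be allocated by then. Baseline is also at discharge. Baseline-first is therefore possible only if allocation waits until about the discharge day, and the window does not ask for that. It allows allocation from the first day of inpatient rehabilitation. Its outer limit can even fall after a discharge at about two weeks from onset. The window is thus tied to neither baseline nor the start of support.

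**3. Bias if knowledge of the arm shifts a baseline.** The ANCOVA estimate is the arm difference at 3 months minus b times the arm difference at baseline, where b is the within-arm slope. If knowing the arm shifts one arm's baseline by s SD, the bias is −b·s. The documents give neither quantity, so both are assumed:

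| Slope b | Shift 0.1 SD | 0.2 SD | 0.3 SD |
|---|---|---|---|
| 0.5 | 0.05 | 0.10 | 0.15 |
| 0.7 | 0.07 | 0.14 | 0.21 |
| 0.9 | 0.09 | 0.18 | 0.27 |

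The entries are absolute bias in SD. The direction depends on which arm shifts and which way.

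**4. Step count.** Let D be the true 3-month effect on steps, and suppose a fraction k of it is already present in the first week after discharge. The covariate then differs between arms by kD, and the adjusted estimate is D − b·kD = D(1 − bk). With k = 0 nothing is lost. At the extreme of k = 1, b between 0.5 and 0.9 leaves 0.5 to 0.1 of the effect. The documents do not give k.

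**5. Patients without a covariate.** Each one is 1/88 = 1.1% of the target. The documents give no rate for loss between allocation and discharge, so a range is assumed on top of the planned 5% dropout. Analysable N is 88 × (1 − loss) × 0.95, and power uses the protocol's f:

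| Loss before discharge | Analysable N | Power |
|---|---|---|
| 0% | 83.6 | 0.806 |
| 2% | 81.9 | 0.798 |
| 5% | 79.4 | 0.785 |
| 10% | 75.2 | 0.763 |

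**The case against.** The strongest reply is that the order is not fixed by the text. The article sets only an outer limit for allocation, and baseline-first fits within it. This is a condensed report, its design flowchart (Figure 1) is not shown, and the day-by-day order of consent, tests and allocation may be set out in the full protocol. No section says when patients are told their arm or who runs the exercise test. Receiving a device after assignment does not place the handover before baseline, and support itself is not said to start before discharge.

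Most of this stands, and it limits the claim. A reader might infer that baselines *are* measured unblinded; the documents show only that they *can* be. That patients know their arm by then is an inference from the absence of blinding and the handover after assignment. But the finding does not rest on silence: the article states both time anchors, and together they allow the wrong order.

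A reader might also infer that every endpoint, the primary included, has an invalid covariate. The documents do not support that. Adverse events use no covariate. eGFRcys, ACR and BNP are laboratory values that knowledge of arm should hardly move. For peak VO2, "the exercise load is terminated when the gas exchange ratio reaches 1.2, which is defined as the peak point", which limits effort effects at the upper end, although a test can still be stopped earlier. EQ-5D has no such protection.

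Nor is the intention-to-treat set shown to be broken. No count of early losses is given, they are probably few, a missing baseline does not by itself remove a patient from the set, and handling of missing covariates is normally left to the analysis plan.

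None of these replies reaches step count. The accelerometer hides its readings from the patient, but that does not undo the fact that support has already begun.

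**Conclusion.** The point holds as a weakness in the stated timing rules. Allocation may precede the baseline exercise test and EQ-5D in an open-label trial, and both then serve as covariates for secondary endpoints. The size of any bias is unknown; 0.05 to 0.27 SD is an illustration that rests wholly on the assumed slope and shift. The primary endpoint is exposed mainly through missing covariates. Even an assumed 10% loss before discharge lowers power, on the protocol's own f, only from 0.806 to 0.763.

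For step count the point needs no inference about who knew what: the stated baseline week follows the start of the intervention, so adjusting for it can understate the effect. How much depends on how early the intervention acts, which the documents do not say. The change is worth making because it is cheap, not because the primary result is shown to be at risk.

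**What to change.** In Randomization and blinding, replace the allocation window with this rule: web allocation takes place at discharge, only after baseline blood, urine, exercise test, grip strength and EQ-5D have been recorded. In Online support for PA management, state that the tracker and app are issued after that. This also closes the gap for patients lost before discharge, since they would not yet be allocated.

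That change alone leaves step count untouched. In Statistical analysis, do not use the post-discharge week as a baseline covariate. Compare 3-month steps adjusted for variables fixed before allocation, such as the allocation factors (age group, sex and peak creatine kinase category). The first-week recording can be kept as a description of early activity.

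**Cost.** The change needs protocol wording only, with no added visit or patient, and N stays at 83 and 88. Support starts at discharge anyway, and the activity pulse and duration targets already "are set according to each patient’s results of the baseline cardiopulmonary exercise test and Karvonen’s formula", so that test has to be available before they are set. The small downside is that device and app set-up moves to the discharge day. Dropping the step-count covariate may cost some precision for that secondary endpoint; the documents give no figure from which to size this.

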### Statistical analysis

In this study, the analysis will involve an intention to treat analysis. Therefore, patients’ consent will be obtained to use 3-month post-assessment information derived from the observed clinical data in the event of dropout or poor adherence in the intervention arm. Regarding background information of participants, discrete data, including frequencies, proportions, and 95% confidence intervals, will be calculated for each group. For continuous data, the mean, standard deviation, and 95% confidence interval will be calculated for each group.

The primary outcome, eGFRcys, will be examined using analysis of covariance (ANCOVA), with adjustment for baseline values as covariates for the least squares mean of eGFRcys at 3 months. Secondarily, between-group comparisons of the change in eGFRcys will be performed in the same way.

The secondary endpoints of ACR, BNP, average number of steps, peak VO2, and EQ-5D will be analyzed using ANCOVA, with adjustment for baseline values. Between-group comparisons of the incidence of adverse events will be performed using the *χ*-square test.

All statistical analyses will be performed using SPSS version 29.0 (IBM Corp., Armonk, NY, USA). Statistical significance will be set at an alpha-level of 0.05.

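### Blinding is ruled out for the whole study although only patients and coaching therapists must know the arm, which leaves an avoidable risk of bias, mainly outside the primary endpoint

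*Protocol article*

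**What the plan says.** Two sections of the Protocol article settle the matter. Study design: "The study design will be an open-label, two-arm, parallel, randomized control trial". Randomization and blinding: "This study will not be blinded". Neither makes an exception for outcome testers, adverse-event classification or analysis.

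The other relevant statements are these:

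- **Primary endpoint** (Outcome assessment): "The primary outcome of this study will be the eGFR based on serum cystatin C (eGFRcys", calculated from a fixed equation. Statistical analysis specifies ANCOVA with baseline adjustment under intention to treat.
- **Retrieved values** (Statistical analysis): consent is sought to use "3-month post-assessment information derived from the observed clinical data in the event of dropout or poor adherence in the intervention arm".
- **Exercise test** (Outcome assessment, text after Table 2): a secondary outcome is "peak oxygen uptake (VO2) based on a symptom-limited cardiopulmonary exercise test (CPET", with a cap: "the exercise load is terminated when the gas exchange ratio reaches 1.2, which is defined as the peak point".
- **Step count** (same place): "the researcher sets the device to prevent displaying the PA data", and "The principal investigator at each hospital will transfer PA data from the accelerometer to the computer".
- **Adverse events** (Statistical analysis): incidence is compared between arms by a chi-square test.
- **Fitbit data** (Table 2): sleep time and heart rate are collected in the intervention group only.

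**The concern.** An open-label intervention does not require that every later step be open. App-based coaching cannot be hidden from the patient or the coach. It can be hidden from whoever prepares and analyses the data, and to some degree from whoever classifies events. By ruling out blinding altogether, the plan gives up protection it could have had.

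Some steps involve judgement: what counts as an adverse event, which data are excluded, what the analyst does where the plan leaves room, and how hard a patient is encouraged in an exercise test. If the person deciding knows the arm, a difference in those judgements looks the same as a treatment effect, and the confidence interval does not cover it. Physical function, and whether the intervention could serve patients who have difficulty attending outpatient rehabilitation, are secondary objectives, so the secondary endpoints carry some of the trial's claims.

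**Working it through.** The blinding statement contains no figure to reproduce, and masking changes neither sample size, alpha nor power. The check is to go through the steps and ask who must know the arm, what the plan already does, and what is left.

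| Step | Must the arm be known? | Protection already in the plan | What remains |
|---|---|---|---|
| Coaching | Yes | None possible | Outside this point |
| Scheduled 3-month eGFRcys | No | Laboratory value, fixed equation, pre-stated ANCOVA, intention to treat | Very little |
| Retrieved 3-month values | No, if one rule covers both arms | ANCOVA and intention to treat fix model and population, not how a value is retrieved | Some: the clause names only the intervention arm |
| Peak VO2 at 3 months | Not by the tester | Cap at gas exchange ratio 1.2 | Encouragement and termination in tests ending below 1.2 |
| Step count | No | Display hidden from the patient | Little at measurement; data handling at site not stated to be masked |
| Adverse events | Not for classification | None stated | Classification with the arm known |
| EQ-5D-5L | Self-reported by unmasked patients | None possible | Assessor masking would not help |
| Exclusions and analysis | No | Pre-stated ANCOVA and intention to treat | Choices those rules do not fix |

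**How far could the retrieval step reach into the primary endpoint?** Inputs from Sample size calculation: 44 patients per arm, 5% dropout, SD 16.0, planning difference 5 mL/min/1.73 m².

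- Dropouts expected in the intervention arm: 0.05 × 44 = 2.2 patients.
- Shift in the arm mean = share of retrieved values × mean error per retrieved value.
- As a yardstick, not an estimate, let every such value be a full planning SD too high: 0.05 × 16.0 = 0.8 mL/min/1.73 m².
- Relative to the planning difference: 0.8 / 5 = 16%.

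So even a deliberately harsh assumption about dropouts moves the primary comparison only modestly. The clause also covers poor adherence, for which the article gives no rate, so the share of retrieved values could exceed 5%. That is a reason to fix the rule for both arms, not evidence of a problem.

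**Would coding the arms be enough alone?** No, for two reasons found in the text. Retrieval tied to poor adherence in the intervention arm reveals the arm to whoever retrieves the value, and a code added to the later dataset does not undo that. Fitbit variables present in one arm only would disclose the code. Both have to be dealt with for the code to work.

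**The case against.** The strongest reply is that nothing here is wrong. The article says open-label in one place and not blinded in another, and these agree. It does not say who runs the exercise test, who classifies events or who analyses the data, and an article may leave such details to the full protocol. This stands as far as it goes: silence about staffing is not a finding. The blinding sentence, however, is not silence. It is a stated decision for the whole study, and its scope can be questioned.

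The reply is also right on several particulars. A reader might infer that bias is actually present, or that the primary result is compromised. The documents do not support either: the endpoint is a laboratory value, the model is pre-stated, and the retrieval clause describes no choice among competing values. A reader might infer that coaches will test their own patients; the article neither says so nor excludes it. A reader might want to attach a false-positive rate to peak VO2. Any such rate would follow entirely from an assumed assessor effect, for which the documents give no figure, and would have to allow for the cap at 1.2, which limits how far encouragement can raise the result.

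Finally, the reply is right that a separate exercise tester is not shown to be free. There are two hospitals and no staffing details. A different tester may also still know the arm.

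**Conclusion.** The point holds as a low-severity, inexpensive improvement. The plan extends non-blinding to steps where knowledge of the arm is not needed, and so leaves an avoidable risk of bias, not a demonstrated one. The risk lies mainly in adverse-event classification, exclusions, analyst choices, and peak VO2 in tests that stop short of the 1.2 cap. The primary endpoint is little exposed; the one opening is the retrieval of 3-month values after dropout or poor adherence. No overall size can be given, because neither an assessor effect nor a rate of poor adherence is stated. The 0.8 mL/min/1.73 m² yardstick rests on the plan's 5% dropout and an assumed error of one SD in each retrieved value. The conclusion assumes that no unseen full protocol already narrows the blanket statement.

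**What to change.** Replace the sentence under Randomization and blinding with:

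> Patients and intervention therapists are not blinded. Retrieval of 3-month clinical values follows one rule applied to both arms. The analysis dataset carries coded arms (A/B) with the intervention-only Fitbit variables held separately, and the code is opened only after retrieved values, exclusions and adverse-event classification are final. Where existing staff allow, the 3-month CPET is not run by the therapist who coached that patient.

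The retrieval clause under Statistical analysis should be reworded to match, so that it no longer names one arm. For the code to protect adverse-event classification, that classification should be made or confirmed from the coded listing.

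The cost is a short protocol change, a recoded arm variable, separate storage of the Fitbit variables and some scheduling effort. The coded analysis needs no extra staff and is worth having even if the exercise tests cannot be rostered differently. The change does not remove bias from patients' own knowledge of their arm, nor unequal detection of events arising from daily symptom monitoring in the intervention arm.
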